### Sample Size Justification

We have conducted a preliminary analysis of the number of AST and platelet count testing events that were performed at St Vincent’s Pathology over a 12-month period (2019). These data showed approximately 11,000 people known to St Vincent’s hospital clinics, and a further 4400 people in the community that had AST and platelet count testing events, that would have allowed APRI calculation to be performed, proving the feasibility of reaching large numbers within the community for cirrhosis screening.

For the comparison of rate of referral for FibroScan before and after the intervention, we estimate that we will be powered to detect a 10% difference in rates of FibroScan referral before and after the intervention. For the logistic regression analyses to determine the difference in proportion of APRI scores leading to referral before and after providing cirrhosis information and FibroScan referral link information (overall and by subgroup), and for determining the proportion of FibroScan referrals that are attended (overall and by subgroup), we are powered to detect a 5% or greater difference between the intervention and historical control groups with power 90% and a sample size of 1100 per subgroup. The above numbers of more than 15,400 individuals having APRI calculations within 12 months suggest that we will be adequately powered to explore our end points including stratified by sex, urban versus rural place of residence, age category, socioeconomic quartile of place of residence, and indication for FibroScan (all of which are expected to have >1000 individuals in each subgroup).

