**Methods:**

We have partnered with a large pathology service in Victoria, Australia, to pilot a population-level liver cirrhosis screening package, which comprises (1) automated calculation and reporting of APRI and FIB-4 on routinely ordered blood tests; (2) provision of brief information about liver cirrhosis; and (3) a web link for transient elastography referral. APRI and FIB-4 will be prospectively calculated on all community-ordered pathology results in adults attending a single pathology service. This single-center, prospective, single-arm, pre-post study will compare the monthly rates of transient elastography (FibroScan) referral, liver cirrhosis diagnosis, and the proportion linked to specialist care in the 6 months after intervention to the 6 months prior to the intervention.

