### Analysis Methods

The number of APRI and FIB-4 scores generated and the proportion of APRI and FIB-4 scores in the cirrhosis range will be described overall and rates per month will be calculated.

The number (proportion) of individuals with an elevated APRI or FIB-4 who are referred for a FibroScan will be described overall and per month; and the number of FibroScan referrals after the intervention will be compared with the number of FibroScan referrals prior to the intervention by logistic regression modeling (time series analysis with the timepoint of interruption defined as February 1, 2024, when the reported APRI score intervention was introduced).

Similarly, the number (proportion) of individuals with an elevated APRI or FIB-4 who are referred for a FibroScan and who attend their FibroScan appointment, overall and per month, will be described and compared with the number (proportion) of FibroScan appointments attended prior to intervention using linear regression modeling, as well as the number (proportion) of individuals with FibroScan results in cirrhosis range that are referred and attend specialist liver clinic appointments.

The number and proportion of individuals with an elevated APRI or FIB-4 who had cirrhosis confirmed by FibroScan will be described, and sensitivity, specificity, and positive and negative predictive values of APRI for cirrhosis determined by confusion matrix. The area under the receiver operating characteristic curve of APRI and FIB-4 for cirrhosis diagnosis will also be calculated by receiver operating characteristic analysis.

The bivariate distribution of sociodemographic (sex, age category, and urban or regional place of residence [defined by postcode using SEIS data]) and clinical variables (liver disease indication) within the proportion of people with elevated APRI and FIB-4 score, who attend FibroScan testing, have elevated FibroScan results, and attend the liver specialist clinic will be determined and compared with their counterparts using chi-square test for categorical data, 2-tailed Student *t* test for parametric continuous data, and Wilcoxon rank-sum test for nonparametric continuous data as appropriate.

A 2-tailed *P* value of .05 will be used as the significance threshold for all analyses. All analyses will be performed using STATA (version 17; Stata Corporation).

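### The 90% power at 1100 per subgroup fits a plain before/after comparison; the named interrupted time series, if it carries a time trend, has far less unless baseline referral is very low

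*Protocol article*

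**What the plan says.** The Sample Size Justification introduces its main power statement with "For the logistic regression analyses to determine the difference in proportion of APRI scores leading to referral before and after" the intervention, and claims it both overall and by subgroup: "5% or greater difference between the intervention and historical control groups with power 90% and a sample size of 1100 per subgroup". It expects the subgroups to be large enough ("all of which are expected to have >1000 individuals in each subgroup"). It gives no baseline proportion, no number of time points, and no allowance for trend or autocorrelation. A separate sentence says the study is "powered to detect a 10% difference in rates of FibroScan referral before and after the intervention", with no power, count or baseline attached.

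The Analysis Methods section compares referrals after and before the intervention "by logistic regression modeling (time series analysis with the timepoint of interruption defined as February 1, 2024"). This is the only logistic regression in that section. Its significance rule is two-tailed: a *P* "value of .05 will be used as the significance threshold for all analyses". The abstract fixes the windows, comparing outcomes "in the 6 months after intervention to the 6 months prior to the intervention".

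**The concern.** The power sentence sizes two independent groups, intervention and historical control. An interrupted time series asks something harder: whether the level shifted at the interruption beyond what the underlying trend would have produced. With six monthly points on each side, step and calendar time are strongly correlated, so much of the information behind a simple before/after difference goes to separating the two. The sample-size text makes no allowance for this.

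What is at stake is how a null subgroup result is read. If the published plan says 90% power and the fitted model has much less, a non-significant step in, say, one socioeconomic quartile would be taken as evidence against a 5-point effect when the analysis could easily have missed it.

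**Working it through.** **Inputs.** Two-sided 0.05 (Analysis Methods). Difference of 5%, read as 5 percentage points; 90% power; 1100 per subgroup (Sample Size Justification). Windows of 6 + 6 months (abstract, Study Timeline). Assumptions: the baseline proportion, which is not stated and is therefore back-solved and varied; equal monthly numbers; an immediate step; no overdispersion or autocorrelation.

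**Step 1: the plan's own figure.** Two-proportion formula, pooled variance under the null:

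n per period = [1.960·√(2p̄(1−p̄)) + 1.282·√(p₀(1−p₀)+p₁(1−p₁))]² / (p₁−p₀)²

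- 13% versus 18%: [1.960·√0.26195 + 1.282·√0.2607]² / 0.0025 = (1.003 + 0.654)² / 0.0025 ≈ 1099. Power at 1100 per period is 90.0%.
- If 1100 is split as 550 + 550: 4.6% versus 9.6% gives 89.9%.

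The stated figure is therefore consistent with a plain two-group calculation. Back-solving shows consistency only; it does not confirm what the sponsor assumed.

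**Step 2: cost of the trend term.** For months 1 to 12 with a step after month 6, the sum of squares is 143 for time and 3 for the step, and the cross-product is 18. Hence R² = 18² / (143 × 3) = 324/429 = 0.755, and the variance inflation is 1/(1 − 0.755) ≈ 4.09. This comes from the layout of the months, not from the baseline.

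**Step 3: power for the step, taking the 90% as given.** 90% power corresponds to a standardised effect of 1.960 + 1.282 = 3.24. With the inflated variance, power = Φ(3.24/√4.09 − 1.96) = Φ(1.60 − 1.96) ≈ 0.36.

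**Step 4: logistic model on 12 monthly binomial points.** Wald power from the information matrix, 1100 per period, 5-point step. In the last column the step is evaluated at the first intervention month.

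| Baseline | Two-group before/after | Trend + step | Trend + step + slope change |
|---|---|---|---|
| 1% | >99% | 94% | 72% |
| 5% | 99% | 61% | 54% |
| 10% | 94% | 42% | 39% |
| 13% | 90% | 36% | 34% |
| 20% | 80% | 28% | 27% |

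At 550 per period and a 4.6% baseline, trend + step gives 37% and the slope-change model 32% (39% and 38% on the linear scale). Simulation at baselines of 10%, 14%, 15% and 20% agreed with the information-matrix results.

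**Step 5: related quantities at the 13% baseline.** Restoring 90% power needs about 4,500 per period (trend + step) or 4,800 (with slope change). Overdispersion of 1.5 or 2 would lower the 36% to 26% or 20%. With no trend term, the logistic model returns to 90%.

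**The case against.** Four counter-arguments deserve weight.

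1. **The trend term is not written down.** The article says only "time series analysis with the timepoint of interruption defined as February 1, 2024"; model terms may sit in a fuller document. The abstract calls the study pre-post, and Primary Outcome Measurement describes a comparison with the preceding 6 months. Without a trend term, power stays near 90%. This stands as a condition on the result. But a time series analysis with a defined interruption ordinarily models time, and if none is intended the label misdescribes the analysis. Either way the two sections need reconciling.

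2. **The two sections name slightly different quantities.** The power sentence concerns the proportion of APRI scores leading to referral; the time-series sentence compares the number of referrals. The link between them is an inference, though a reasonable one, because only one logistic regression of referral is described.

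3. **The baseline could be very low.** Before the intervention, 446 individuals had elevated APRI and 816 elevated FIB-4, at most 1262/37,872 = 3.3% of those tested. The outcome definition also counts referrals through a link introduced with the intervention. At a 1% baseline and 1100 per period, the trend-plus-step model reaches 94%. This stands, and it is why a single figure near 36% cannot be presented as the study's power. Even at 1%, power is 72% with a slope change; with 550 per period it is 70% and 43%.

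4. **The overall comparison is much larger.** A reader might infer that the whole referral analysis is underpowered. The documents do not support that: with 37,872 individuals per period, power for a 5-point step is essentially 100% at every baseline tried. If only those with elevated scores count, numbers are far smaller, but that turns on the choice of denominator.

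A reader might also infer that the 10% rate claim is wrong. It gives no power, count or baseline, so it cannot be shown wrong; it is simply unsupported as it stands.

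**Conclusion.** The point holds in a limited form. The stated 90% power at 1100 per subgroup is that of a two-group before/after comparison, while the analysis named for referral is an interrupted series of 6 + 6 months. If that series is modelled with a trend, a design with 90% before/after power has about 36% for the step (32% to 39% across the model variants and the 1100 and 550 readings). At 1100 per period the figure depends on the unstated baseline and falls well short of 90% at 5% and above; near 1% it meets 90% only without a slope-change term.

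No stated number is miscalculated. The fault is that the power statement and the named analysis do not match. The point is confined to the subgroup claim for referral; it does not extend to attendance, which the Analysis Methods assign to linear regression without naming a time series. It should be corrected because it affects how null subgroup findings are read.

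**What to change.** In the Sample Size Justification, state the assumed baseline referral proportion, the denominator, and whether 1100 is per period or in total. Then do one of the following:

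- (a) say that the 5%/90%/1100 figure applies only to the unadjusted before/after comparison of proportions, name that as the powered analysis, and report the interrupted time series alongside with its confidence interval; or
- (b) restate the power, or the detectable step, for the trend-adjusted 6 + 6-month model.

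In either case, label subgroup time-series results exploratory. For the 10% rate claim, give its basis (power, baseline count, model) or limit it to the before/after comparison.

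The cost is a less favourable stated power. No extra patients, data or visits are needed.

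### Before-after effects are to be compared by subgroup at .05 with 90% power claimed per subgroup; within-stratum significance cannot show that effects differ, and the document does not support the power figure

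*Protocol article*

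**What the plan says.** The by-subgroup commitment stands in the Protocol article, Sample Size Justification. It names two before-after analyses. One is the proportion of APRI scores that lead to referral, "after providing cirrhosis information and FibroScan referral link information (overall and by subgroup"). The other is "for determining the proportion of FibroScan referrals that are attended (overall and by subgroup"). For both, the study is said to be "powered to detect a 5% or greater difference between the intervention and historical control groups". That claim comes "with power 90% and a sample size of 1100 per subgroup". The section closes by saying that more than 15,400 people with a calculable APRI over one year "suggest that we will be adequately powered to explore our end points including stratified by sex, urban versus rural place of residence, age category", indication for FibroScan and socioeconomic quartile, and that each subgroup should hold more than 1000 people.

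Analysis Methods sets the threshold: "A 2-tailed *P* value of .05 will be used as the significance threshold for all analyses". It describes the before-after models without mentioning subgroups. Separately, it plans chi-square, t or rank-sum comparisons of sociodemographic and clinical variables between people with and without each outcome, at the same threshold.

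**The concern.** Sizing each subgroup for its own before-after difference, and judging everything at .05, invites one significance verdict per stratum. Such verdicts do not answer the subgroup question. Whether the programme works differently in, say, urban and regional residents depends on the difference between the two stratum effects, and that comparison is neither described nor what the power statement covers. Two errors can follow. With no effect anywhere, some stratum may cross .05 by chance. With the same effect everywhere, some strata will cross .05 and others will not, and the pattern can be read as the programme working only in certain groups. A claim of 90% power in each subgroup makes both misreadings more credible, so the basis of that claim also matters.

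**Working it through.** **1. The plan's own figure.** Inputs from Sample Size Justification and Analysis Methods: 90% power, two-sided .05, a 5% difference (read here as 5 percentage points), 1100 per subgroup. The article states neither the baseline proportion nor whether 1100 is per period. For two proportions,

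n per period = [1.960·√(2·p̄(1−p̄)) + 1.282·√(p1(1−p1) + p2(1−p2))]² / (p2−p1)².

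With p1 = 0.13 and p2 = 0.18 (p̄ = 0.155): [1.960×0.5118 + 1.282×0.5106]² / 0.0025 ≈ 1,099. So 1100 per period is reproduced for a baseline of about 12.5-13.5%, or the mirror range near 82%. If 1100 covers both periods (550 each), only a baseline of about 4-5% fits. At 1100 per period, power is 99% at a 5% baseline, 80% at 20%, 71% at 30% and 65% at 45-50%.

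**2. Are the numbers there?**
- The calculation needs 1100; the text expects more than 1000.
- The 15,400 is 11,000 + 4,400. The 11,000 (71%) are people known to the hospital's clinics, whereas Recruitment excludes inpatient tests and tests requested by hospital outpatient services.
- Results reports 37,872 eligible individuals, so the number of people scored is not the constraint. The denominator is. Elevated scores occurred in 446 people (APRI) and 816 (FIB-4), so at most 446 + 816 = 1,262 people if none had both.
- If the comparison is among people with an elevated score, as Analysis Methods words it, a two-level factor needs 2 × 1100 = 2,200 per period, or 1,100 on average if the figure covers both periods. Four quartiles would average at most 1,262/4 ≈ 316 in the preintervention data.
- If the denominator is everyone scored, referring every person with an elevated score gives at most 1,262/37,872 = 3.3%. A rise of 5 points could not come from elevated scores alone.
- Attendance is a proportion of referrals. The article gives no number of referrals.

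**3. False positives with no effect.** Stated or implied levels: sex 2, residence 2, socioeconomic quartile 4, so 8 strata.
- One end point, independent tests: 1 − 0.95⁸ = 0.34. Two end points: 1 − 0.95¹⁶ = 0.56.
- The same people appear under each factor. A simulation of equal-sized crossed strata (40,000 replicates) gives 0.28 for one end point. For two, taken as independent, 1 − (1 − 0.284)² = 0.49.
- Adding assumed levels (6-8 age bands, 3-6 indications) makes 17-22 strata: 50-61% with overlap or 58-68% under independence for one end point, and 75-85% or 83-90% for two.

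**4. Discordance with a uniform effect.** Strata of one factor contain different people. At the article's 90% power in each:
- exactly one of two significant: 2 × 0.9 × 0.1 = 18%;
- at least one of four not significant: 1 − 0.9⁴ = 34%.

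**5. What interaction tests would do.** Five factors give five tests per end point: 1 − 0.95⁵ = 23%, or 1 − 0.95¹⁰ = 40% for two end points, unadjusted and taken as independent. With 1100 per period in each of two strata, power to detect a 5-point effect in one stratum and none in the other is about 93% at a 5% baseline, 53% at 20% and 43% at 30%.

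**The case against.** The strongest reply is that this is a condensed article about a pilot. Interaction terms, multiplicity rules and the status of subgroup analyses commonly sit in an analysis plan that is not shown. The secondary objective is descriptive, the hypothesis contains no subgroup claim, and the subgroup sentence uses the verb explore. Much of this stands. A reader might infer that leaving out an interaction test is itself an error, or that the subgroup work is presented as confirmatory. The article supports neither. Nor does it say outright that a separate model will be fitted in each stratum: the by-subgroup wording does not settle the model form. What remains is what the article does fix: a power statement for the difference within each subgroup, and .05 for all analyses. The word explore sits inside a claim of adequate power and exempts nothing from that threshold.

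Two larger readings should also be set aside. If 90% power is placed on the overall comparison, two equal strata would have 63% power each and disagree 47% of the time. The article claims 90% per subgroup, so 18% is the figure on its own terms. Nor do the sociodemographic comparisons in Analysis Methods share the within-stratum fault: they already compare groups directly and need no interaction term.

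**Conclusion.** The concern holds in a limited form. Comparing before with after inside each subgroup at .05 cannot establish that effects differ between subgroups, and the power claimed is for that within-subgroup comparison. The risk of a chance finding is 28-34% for one end point and 49-56% for two on the 8 strata whose levels are stated or implied. Higher figures depend on assumed numbers of age bands and indications, so a reader should not conclude that a false positive is more likely than not for a single end point on the stated levels. The two-end-point figures treat the end points as independent, and the lower figure of each pair assumes equal-sized strata.

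The claim of 90% power per subgroup is unsupported rather than disproved. Without a baseline it can be neither confirmed nor refuted as a formula. However, the stated subgroup size, the make-up of the 15,400, the referral denominator for attendance and the preintervention counts of elevated scores do not sustain it as a blanket statement. Those counts are as of January 2024 and may not cover the full six months. That subgroup results would steer a roll-out is a possible consequence; the article does not say so.

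**What to change.** In Analysis Methods and Sample Size Justification:

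- Assess each subgroup factor by one period-by-subgroup interaction term in the model used for the same end point, and report every stratum's estimate with a 95% CI.
- State that subgroup results and the bivariate sociodemographic comparisons are exploratory and are not judged against .05 as stand-alone findings. The bivariate comparisons need only this label.
- Remove the claim of 90% power in each subgroup, or restate it with the baseline proportion, the denominator for each end point, whether 1100 is per period, and the eligible numbers expected.

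The cost is wording and one extra model term per factor; no new data are needed. The downside is small but real. Interaction tests have low power at all but low baselines, and subgroup results can no longer be reported as significant in their own right. Because five unadjusted interaction tests still carry about a 23% chance of a false positive per end point, the exploratory label is needed as well as the change of method.

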#### Exposure Variables Collected

Sex, age category (deciles), socioeconomic status of residence (defined by Australian Bureau of Statistics Socio-Economic Index Areas [SEIS] data matched to postcode), urban versus regional place of residence (defined by SEIS data matched to postcode), and liver disease indication recorded on FibroScan requests will be collected.

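### Indication for FibroScan is known only for people with a request, so it cannot stratify the proportion referred or be compared between tested people with and without elevated scores

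*Protocol article*

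**What the plan says.** Exposure Variables Collected gives one source for the only clinical variable: "liver disease indication recorded on FibroScan requests will be collected". No other section names a second source. Strengths and Limitations concedes that routine pathology data carry few clinical variables.

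Sample Size Justification plans logistic regression for two outcomes. One is the "difference in proportion of APRI scores leading to referral before and after providing cirrhosis information and FibroScan referral link information (overall and by subgroup"; the other is "determining the proportion of FibroScan referrals that are attended (overall and by subgroup". The next sentence claims adequate power for the end points "stratified by sex, urban versus rural place of residence, age category, socioeconomic quartile of place of residence, and indication for FibroScan". It bases this on "more than 15,400 individuals having APRI calculations within 12 months" and says of the subgroups: "all of which are expected to have >1000 individuals in each subgroup".

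Analysis Methods lists, for bivariate comparison with counterparts, sociodemographic variables and "clinical variables (liver disease indication) within the proportion of people with elevated APRI and FIB-4 score, who attend FibroScan testing", followed by elevated FibroScan result and liver clinic attendance. Indication is thus named for four steps of the cascade, the first being the elevated score itself.

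**The concern.** The indication field comes into existence when someone completes a FibroScan request. Two of the planned uses treat it as if every tested person had a value.

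The first use is as a subgroup for whether a score leads to referral. Membership of the subgroup then presupposes a request, which is the event being counted.

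The second use is the comparison of indication between people with and without elevated scores. It can be made only among people with a request. Under Comparator Group (Standard of Care) and Preintervention Period, scores are withheld from clinicians until February 1, 2024. Under Intervention Period, the report then recommends FibroScan for an elevated score. Who enters the comparison therefore depends on the score, and differently in the two periods.

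At stake are a subgroup result that does not answer its question, and an apparent link between liver disease type and elevated score that may partly reflect referral behaviour.

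**Working it through.** **The plan's own figure.** Sample Size Justification states 1100 per subgroup, 90% power and a 5% difference, with two-sided alpha .05 from Analysis Methods. No baseline proportion is given. The formula is n = [1.960·√(2p̄q̄) + 1.282·√(p₁q₁ + p₂q₂)]² / (p₂ − p₁)². For 13% versus 18%, p̄ = 0.155 and n = (1.0031 + 0.6543)² / 0.0025 = 1099 per period. The pair 82% versus 87% also gives 1099, while 5% versus 10% gives 582 and 20% versus 25% gives 1464. So 1100 can be reached, but only at an unstated baseline. This does not affect the point below, because more people do not help when the stratum is defined by the request.

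**Check 1: proportion referred within an indication stratum.** There are three ways to count.
- *Per person, any referral.* Everyone in the stratum has a request, so referred/total = 1 before and 1 after. The difference is 0 and the logistic model has no outcome variation.
- *Per person, online referrals only.* Outcome Measures counts referrals made through the pathology link, whereas preintervention requests are faxed. If indication is read from both kinds of form, the quantity is online/(online + fax). That is about 0 before, because the link is not yet in use, and at most 1 after. It describes the route of a request.
- *Per score.* Results gives 42,025 tests on 37,872 individuals, or 42,025/37,872 = 1.11 per person. If people with a request had this average and exactly one score each led to referral (an assumption), the proportion would be 37,872/42,025 = 90.1%. That figure reflects how often people are retested.

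Under all three, the denominator leaves out every tested person without a request.

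**Check 2: how many tested people lack the variable.** The article gives no referral count. Assuming 200 to 1,000 of the 37,872 individuals have a request, the share without an indication is 1 − 1000/37,872 = 97.4% to 1 − 200/37,872 = 99.5%.

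**Check 3: subgroup size.** With k indication groups of more than 1000, more than 1000·k people with a request are needed: over 2000 for two groups and over 4000 for four. The 15,400 cited are tested people. For scale, at most 446 + 816 = 1262 individuals had an elevated APRI or FIB-4 in the preintervention data. This is not a ceiling on referrals, since people without elevated scores can also be referred.

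**Check 4: can conditioning on referral distort the comparison?** Let indication type (A or B) and elevated score be independent among all tested people, so the true odds ratio is 1.0. Among referred people the odds ratio becomes (r_A,elev · r_B,non) / (r_A,non · r_B,elev), where r is the probability of referral.
- Assume referral of 30% for elevated scores of either type, and 5% (A) or 1% (B) for non-elevated scores. The odds ratio is (0.30 × 0.01)/(0.05 × 0.30) = 0.20. With 30% type A in the population, type A is 30% of referred people with an elevated score and 68% of referred people without one.
- Assume instead 20% and 2% for type A, and 10% and 1% for type B, so that score and type act multiplicatively. The odds ratio is (0.20 × 0.01)/(0.02 × 0.10) = 1.0, with no distortion.

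All these referral rates are invented. They show that bias is possible and give no estimate of it.

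**The case against.** The strongest reply is that the plan never says every subgroup is crossed with every outcome. The list of subgroups stands in a general sentence about end points, and indication is a proper stratifier for attendance among referred people. The secondary objective and secondary outcomes concern sociodemographic factors only, and in Analysis Methods indication is valid for three of the four steps. On this view, which subgroup goes with which outcome is detail for the full plan.

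Part of this stands. The later steps are sound and the affected analyses are not central. But the by-subgroup wording is attached to both outcomes, the one list of subgroups follows directly, and Analysis Methods names the elevated score explicitly. Nothing limits indication to outcomes after referral. The difficulty lies in what is stated and does not depend on missing detail.

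A reader might also infer that the stratified referral proportion must be exactly 100% in both periods under any definition. The article does not support that: it counts online-link referrals and provides for analysis per test event, and either can bring the figure below 100%.

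**Conclusion.** The point holds. As written, two analyses use a variable that exists only for people with a request. The stratified referral proportion cannot be a referral rate among tested people under any of the plan's ways of counting, and per person with any referral it is 100% in both periods. The expectation of more than 1000 per indication subgroup rests on the wrong population.

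The elevated-versus-not comparison of indication may be biased. A reader might go further and call it biased by construction, but the article gives no referral rates, the size and direction are unknown, and the bias vanishes if score and indication act multiplicatively on referral. The 97.4% to 99.5% without a value likewise rests on an assumed referral count.

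The consequence is limited to one exploratory subgroup and one step of a secondary bivariate description. The overall pre-post comparisons are untouched, as is the use of indication for attendance, cirrhosis-range result and linkage to the liver clinic. The conclusion assumes that the request form is the only source of indication, as the article states.

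**What to change.** In Sample Size Justification, remove indication for FibroScan from the subgroups for the proportion of scores leading to referral, and stop basing its expected subgroup size on tested people. If a size is wanted for indication groups, derive it from the expected number of referred people.

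In Analysis Methods, remove liver disease indication from the comparison of people with and without elevated scores.

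Keep indication for outcomes after referral and name the denominator: referred people for appointment attendance, scanned people for a cirrhosis-range result, and scanned people with a cirrhosis-range result for linkage to the liver clinic.

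The cost is a wording change. What is lost is a subgroup analysis that could not answer its question and a comparison that could not be read as applying to tested people.
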